**5.0 STUDY POPULATION**

Thirty-six healthy women will be enrolled in this study. Participants will be selected for this study and recruited according to the criteria below. Conditions for withdrawal from the study are described in Section 12.

Subjects will be recruited from the catchment area of the MMC, which is centered around 2 hospital campuses, the Montefiore Hospital and the Weiler Hospital. There is a diverse ethnic distribution consisting of 48% Hispanics, 36% Blacks and 7% Whites. The diversity of the population in our catchment areas permits the recruitment of patients from most of the major ethnic groups including Asians and Pacific Islanders, Blacks, Hispanics from Mexico, Puerto Rico, Cuba and Central and South America and Caucasians.

The study will be conducted at the General Clinical Research Center (GCRC) at the AECOM and MMC. Providers from the Internal Medicine, Adolescent and Gynecology Clinics at MMC will refer participants. IRB-approved advertisements will be posted to recruit self-referrals. Potential subjects will contact the study staff to discuss the details of the study, including inclusion criteria, and to schedule screening appointments.

# 5.1 Participant Inclusion Criteria

# Women who meet all of the following criteria (by self-report, unless otherwise specified) are eligible for inclusion in this study:

- Age between 18 and 50.
- Able and willing to provide written informed consent to participate in the study.
- Normal menstrual history with regular cycles with a minimum of 21 days between menses.
- Low risk for HIV/STI infection. Low risk is defined as

1. Not having had an STI in the last 6 months.
2. Not having used non-therapeutic intravenous drugs in the last year.
3. Being either sexually abstinent or being in a stable, mutually monogamous relationship with a partner who is not known to be HIV positive.

- Agree to the insertion of Acidform lubricant or HEC gel.
- Agree to abstain from vaginal and anal intercourse and to not use vaginal products for 48 hours prior to enrollment and for the duration of the study (through the Final Visit).

# 5.2 Exclusion Criteria

Women who meet any of the following criteria (by self-report, unless otherwise specified, at screening, enrollment, or at anytime during participation, unless otherwise specified) will be excluded from this study:

- Are pregnant (based on a serum or urine pregnancy test) or less than 6 months post-partum.
- Are currently breastfeeding.
- Are menopausal.
- Are currently using hormonal contraception or have used hormonal contraception in the previous 2 months.
- Are currently menstruating (at screening or enrollment visits – may be eligible for deferment).
- Are currently participating in a research study of other vaginal products.
- Have a positive HIV test at screening.
- Have a urinary tract infection at screening (may be eligible for re-screening after treatment).
- Have a positive chlamydia, gonorrhea, or trichomonas result at screening.
- Have an abnormal Pap test (if documentation of a negative result within the past year is not available).
- Have a clinically detectable genital abnormality (i.e., vulvar, vaginal, cervical and/or perianal ulcer and/or lesion or an abnormal wet mount).
- Have a history of intermenstrual bleeding in the 3 months prior to enrollment.
- Have had gynecological surgery or received treatment for syphilis, genital herpes, chlamydia, gonorrhea, trichomonas, or genital warts in the last 6 months.
- Have received treatment for candida, bacterial vaginosis, or urinary tract infection in the prior month.
- Have douched or used any vaginal products**,** including lubricants, feminine hygiene products, vaginal drying agents and sex toys during the 48 hours prior to enrollment.
- Have had vaginal or anal intercourse during the 48 hours prior to enrollment.
- Oral or intravenous antibiotics in the 7 days prior to enrollment.

**6.0 STUDY PRODUCT/INTERVENTION(S)**

**6.1 Regimen**

Study staff will review the administration of Acidform lubricant or HEC gel with each participant at her Enrollment Visit. At the Enrollment Visit, the participant will insert a 5 gram (equal to 5 ml) dose of Acidform lubricant or HEC gel vaginally to a depth of approximately 6 cm under the guidance of the study clinician. The volunteers will insert subsequent applications twice daily for a dosing total of 14 days. Participants will be instructed on proper insertion technique and storage requirements (see Appendix III).

**6.2 Study Product Formulation and Preparation**

**Acidform**

Acidform is an acid buffered gel (pH = 3.5) containing three buffering agents (citric acid, potassium bi-titrate, and lactic acid). It is dense, viscous, off-white, and uniform with an acidic flavor (8). The acid-buffering properties of Acidform gel maintain the acidic vaginal milieu (pH = 3.5-4.5) even in the presence of semen, making the gel spermicidal. Its antimicrobial action towards herpes and chlamydia have been established through animal studies using Acidform gel without N-9 (7).

Product should be stored at controlled room temperature until required for administration. Controlled room temperature is defined as 25 degrees Celsius (°C)/ 77 degrees Fahrenheit (°F). Excursions are permitted to 15°C to 30°C (59°F to 86°F).

**HEC**

The placebo for this study is hydroxyethylcellulose (HEC) gel. HEC gel is a water-based gel formulation designed for use as an inert comparator in clinical trials of candidate vaginal microbicides for the prevention of STI, including HIV infection. HEC gel was designed to neither increase nor decrease the risk of HIV infection, but to sufficiently match the physical properties of candidate active products so as to control for behavioral confounders in clinical trials. The formulation was developed by [name] (ReProtect, Inc.) and will be provided by Instead Healthcare, LLC.

HEC gel is similar in appearance and physical properties as the marketed over-the-counter vaginal lubricant K-Y Jelly (McNeil-PPC, Inc.). All ingredients used in the manufacture of HEC gel are compendial (United States Pharmacopeia/National Formulary) and are generally recognized as safe for use in topical pharmaceutical preparations. Hydroxyethylcellulose is used as a gel thickener. HEC gel was made isotonic (with sodium chloride) to reduce the risk of epithelial damage caused by cell swelling or dehydration. The formulation was also made slightly acidic (pH 4.4) to avoid disrupting the normal vaginal pH. Buffering capacity, however, is minimal. Sorbic acid was selected as a preservative based on its safety profile and lack of activity against HIV *in vitro*.

Placebo gel must be stored at controlled room temperature at all times. Controlled room temperature is defined as 25 degrees Celsius (°C)/ 77 degrees Fahrenheit (°F). Excursions are permitted to 15°C to 30°C (59°F to 86°F).

**6.3 Study Product Supply, Packaging and Accountability**

Instead Healthcare, LLC will provide Acidform lubricant, HEC gel and applicators for this study. Acidform lubricant and HEC placebo gel will be prepared in compliance with Good Manufacturing Practice (GMP) regulations for Instead Healthcare, LLC by Swiss-American Products, Inc, Carrollton, TX.

Study gel (Acidform or HEC) will be packaged in cartons containing 30 pre-filled plastic applicators. The AECOM Research Pharmacist will randomly allocate Acidform or HEC gel in a 1:1 fashion (i.e., 18 subjects per arm).

The pharmacist will maintain an accurate inventory and accountability record of study products received and subsequently dispensed. After the study is completed (or otherwise terminated), all unused study product will be shipped to Instead Healthcare, LLC for destruction. Participants will be dispensed thirty pre-filled applicators of study product at the Enrollment Visit. All product, used and unused, will be returned by the participants to AECOM or MMC. The subjects will be counseled that they are to apply 28 doses of drug or placebo. They will be instructed that they will be given 2 extra doses of drug or placebo to use only if a dose is dropped or lost.

6.4 Assessment of Participant Adherence with Study Product/Intervention(s)

The first application of investigational product will be done at the Enrollment Visit by the participant under the guidance of the study clinician. Participants will be instructed to apply the assigned investigational product at bedtime and twice daily for 13 subsequent days (see Appendix III). For study visits conducted on Day 7 and 14, subjects will be instructed to apply the morning dose after the study visit is completed.

Participants will be asked to record information on the number of times they administer study gel, time of each insertion, and emergence/resolution of specific symptoms in a study diary. Diaries will be reviewed at each visit.

Non-adherence will be defined as three or more days (out of 14) of missed product use. Participants who miss less than three days will (if practical according to their expected date of menses onset) be asked to apply product for additional days to attempt to achieve a full 14 days of product exposure. An additional participant will be recruited for each non-adherent participant. Participants who are non-adherent with the study protocol will be asked their reasons for non-adherence and this information will be recorded on the applicable study forms. Study procedures for Day 7, Day 14, and the Final Visit will be re-scheduled as necessary. Participants will be instructed to call the study staff in the event of missed doses to re-schedule study visits.

Participants will be instructed to abstain from sexual relations throughout the course of the study. To assess whether intercourse occurred, a wet mount will be performed to look for sperm and a vaginal swab will be collected and tested for the presence of semen using the ABAcard p30 test. The test is an antibody immunoassay that detects p30, a glycoprotein produced by the prostate, which is present in human semen. p30 is detectable in the vaginal tract up to a maximum of 2 days. If a participant is found to have engaged in anal or vaginal sexual relations or experienced vaginal penetration with anything other than the study gel applicator throughout the study, this information will be recorded on applicable case report forms. Participants who are non-adherent to sexual abstinence on more than one occasion will discontinue product use. An additional participant will be recruited for each non-adherent participant.

A participant with a clinical toxicity outcome (see Appendix IV) who is discontinued from further product use will be considered to have reached a study endpoint and will not be replaced. Standard clinical care will be provided and followed to resolution.

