## 10.0 STATISTICAL CONSIDERATIONS

## 10.1 Overview and Statistical Designs Issues

## All subjects who receive treatment (Acidform lubricant or HEC placebo gel) will be included in all analyses. The primary objective of this study is to compare the safety of Acidform lubricant to HEC gel by assessing the genital tract mucosal response to 14 days of twice daily application by measuring endogenous antimicrobial activity and levels of mediators of host defense, including defensins, cytokines and chemokines in CVL. The clinical safety of Acidform when administered twice daily for 14 consecutive days will be assessed by also including the following endpoint: Grade 2 or higher adverse experiences judged by the Investigator to be possibly, probably, or definitely related to product use.

Differences between groups with respect to age and baseline amounts of immune mediators will be compared by *t* test. Differences between groups with respect to endogenous antimicrobial activity of CVL against HSV and *E. coli* and change in mucosal immune mediators will be compared by analysis of covariance and adjusted for baseline (after log transformation of data for cytokines, chemokines, and mucosal mediators). Differences between groups with respect to change in percentage reduction in viral or bacterial infection after application of drug or placebo gel relative to titers in screening CVL samples will be determined by Wilcoxon nonparametric test (with exact p-values).

All visits in which a woman has been exposed to the study product will be included in the analysis of clinical safety. The number and the percentages of participants experiencing at least one Grade 2 or higher AE, and the number and percentage experiencing each specific AE will be tabulated by study arm. Each participant will contribute once in each category (i.e. only for highest severity AE for each participant) for the calculation of event rates. The number and percentage of participants experiencing a Grade 2 or higher AE will be tabulated by severity and relationship to treatment for each treatment group. AEs that lead to study product discontinuation will be listed in a separate data listing. The number and percentage of participants with a Grade 2 or higher AE judged possibly, probably or definitely related to study treatment will be summarized and compared for each treatment group by Fisher’s exact test.

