**10.2 Sample Size Considerations**

There is limited data regarding intra- and inter-subject variability of endogenous antimicrobial activity detectable in CVL. We recently completed a pilot study that included measuring endogenous antimicrobial activity and immune mediators in CVL collected weekly for 2 months from healthy women who were either naturally cycling or receiving hormonal contraception. Among 9 cycling women, the mean percentage inhibition of HSV infection (defined as the viral plaque formation in cells treated with CVL as a percentage of plaque formation in the presence of control fluid) at the initial visit was 54 with a standard deviation (sd) of 28. The sd is the same if we use the mean of all samples collected from the cyclers (n=52). If we assume that Acidform and HEC have no impact on endogenous anti-HSV activity and consider 28 (1 sd) as functionally equivalent, a sample size of 18 subjects per arm will provide 80% power to observe statistically significant equivalence of means. This sample size is similar to other Phase I studies of topical microbicide products.

The following table represents the probability of observing zero, at least one, and two or more adverse experiences among the sample size of 18 using Acidform for various “true” event rates:

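### Non-adherence is counted in missed days under a two-dose-a-day regimen, and with every treated woman kept in all analyses no comparison among adequately exposed women is planned

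*Protocol*

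**What the plan says.** Protocol Section 6.3 sets the regimen in doses: "The subjects will be counseled that they are to apply 28 doses of drug or placebo". Section 6.4 gives the same total. After the supervised clinic dose, participants are to "apply the assigned investigational product at bedtime and twice daily for 13 subsequent days", which makes 2 + 13 × 2 = 28 doses.

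Section 6.4 then sets the adherence rule in days: "Non-adherence will be defined as three or more days (out of 14) of missed product use". Two actions hang on that rule. For women above the threshold, "An additional participant will be recruited for each non-adherent participant". Women below it will, if their expected menses allow, "be asked to apply product for additional days to attempt to achieve a full 14 days of product exposure".

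Section 10.1 fixes one analysis set: "All subjects who receive treatment (Acidform lubricant or HEC placebo gel) will be included in all analyses". It names no set based on adherence. The tests listed there are analysis of covariance and the Wilcoxon test for the lavage endpoints, and Fisher's exact test for adverse events. All are tests of difference.

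Section 10.2 argues the sample size from equivalence. It assumes no true effect on anti-HSV activity and an sd of 28, says to "consider 28 (1 sd) as functionally equivalent", and arrives at 18 per arm for 80% power.

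Dose-level data will exist. Section 6.4 says: "Participants will be asked to record information on the number of times they administer study gel, time of each insertion". The Day 7 and Day 14 procedures in Section 7.1 add tube counts and an adherence review.

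**The concern.** A rule counted in days does not classify a woman who uses one of her two daily doses. Staff could apply it in different ways, and Section 10.3 says the clinical team knows each woman's arm. The rule decides who is replaced and who is asked to extend dosing, so the ambiguity has consequences.

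The second problem is how replacement and the analysis set fit together. Recruiting an extra woman for each non-adherent one makes sense if the aim is 18 adequately exposed women per arm. Section 10.1 then keeps the non-adherent woman in every analysis, and no comparison uses the exposed women alone. Because the first dose is supervised, a woman who used only that dose counts fully in the 14-day comparison.

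If Acidform does reduce mucosal defence, under-dosed women shrink the observed difference. In a safety trial sized to show equivalence, that shift favours the reassuring conclusion.

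**Working it through.** **1. What the adherence rule allows**

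- *Reading A: a missed day means no product at all.* A woman may miss two whole days (2 × 2 = 4 doses) and one dose on each of the other 12 days (12 doses). That is 16 missed and 12 of 28 used, 12/28 = 43%, and she is adherent. With 17 missed, at least 17 − 14 = 3 days must be wholly missed, so only from 17 is she certain to be non-adherent.
- *Reading B: any missed dose makes a missed day.* Three single doses missed on three days make her non-adherent with 25/28 = 89% used.

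The threshold thus runs from 3 to 17 missed doses.

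**2. Reproducing the sample size**

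Inputs from Section 10.2: sd 28, margin 28, true difference 0, power 80%. Alpha is not stated; I assume two one-sided tests at 0.05 each.

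- n per arm = 2 × (sd/margin)² × (z0.95 + z0.90)² = 2 × 1 × (1.645 + 1.282)² = 17.1, so 18.
- At one-sided 0.025: 2 × (1.960 + 1.282)² = 21.0, which rounds up to 22.
- Simulated power of the t-based procedure at n = 18: 80%.

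The stated 18 is reproduced at one-sided 0.05.

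**3. Effect of dilution**

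Assumptions, none of them in the protocol: the true loss in full users equals the margin (28 points); missing doses is unrelated to outcome; k Acidform women are under-dosed and get a fraction e of the effect. Where women are replaced and kept, each arm has 18 + k women. The observed mean difference is 28 × (18 + k·e)/(18 + k).

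| Acidform arm | e | Mean difference | False equivalence |
| --- | --- | --- | --- |
| 18, none under-dosed | – | 28.0 | 5.0% |
| 3 of 21 | 11/14 | 27.1 | 6.1% |
| 3 of 21 | 1/2 | 26.0 | 7.6% |
| 3 of 21 | 0 | 24.0 | about 11% |
| 4 of 22 | 0 | 22.9 | about 13% |

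The value e = 11/14 is a woman who just meets the threshold with three whole days missed, with effect proportional to days used.

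Hand check of the row with 3 of 21 and e = 0: the standard error is 28 × √(2/21) = 8.64, and Φ((28 − 24)/8.64 − 1.645) = Φ(−1.18) = 12%. The simulation gives slightly less because mixing exposed and unexposed women widens the spread.

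**4. Under a difference test**

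I use a two-sided t-test at 0.05 as a stand-in for the planned tests, with the same 28-point loss in users:

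- 18 per arm, none under-dosed: 83%.
- 3 of 21 wholly unexposed: 75%. With nobody under-dosed, 21 per arm would have about Φ(28/8.64 − 1.96) = Φ(1.28) = 90%.
- 4 of 18 wholly unexposed, not replaced: mean difference 28 × 14/18 = 21.8, power 59%.
- Leaving those 4 women out: power 78%, and false equivalence back from 14% to 5%.

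**The case against.** The strongest reply is that equivalence appears only in the sample-size argument. The planned tests are tests of difference, so a false-equivalence rate describes a test that the protocol does not specify. This stands. Under the plan as written the cost is lost power, and it becomes a wrong reassurance only if a non-significant result is read as safe.

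A reader might infer that the error rate of this trial is 12%. The documents do not support that. They give no under-dosing rate, and the figure needs 3 of 21 women with no effect at all. Women just over the threshold may have used gel on 11 of 14 days, and then the rate is about 6%. If there is no true difference, dilution moves nothing.

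A reader might also translate the rule into 6 or more of 28 doses missed. That matches neither reading of the text, and the rule also governs make-up dosing, so the protocol team must reconcile it.

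The protocol has safeguards: make-up days, diaries, tube counts and reminders. They help, but make-up dosing covers only women under the threshold and only where practical.

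The all-treated set is proper for adverse events and for a Phase I safety comparison, and an adherent-set analysis is often left to a statistical analysis plan, which is not at hand here. Nothing forbids adding one. Still, Section 10.1 does not leave the matter open: it assigns one set to every analysis.

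Finally, an adherent set can itself hide harm if women skip doses because of symptoms. That is a good reason not to make it primary.

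**Conclusion.** The point holds, at moderate weight. The adherence rule is ambiguous across a range of 3 to 17 missed doses. The protocol replaces non-adherent women but plans no analysis that uses the exposed women alone.

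The size cannot be fixed from the documents. Under the assumed range, false equivalence would be about 6% to 11% with 3 of 21 under-dosed and about 13% with 4 of 22 wholly unexposed, against 5%. Under a difference test, power would be 75% with 3 of 21 and 59% with 4 of 18 wholly unexposed, against 83% at 18 per arm undiluted. These figures rest on sd 28, a true 28-point loss in users, one-sided 0.05 for the equivalence test, and dose-skipping unrelated to outcome.

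It would go too far to say that the trial is biased towards equivalence as such. The direction is clear only if a true difference exists, and the extent depends on a rate that the protocol does not give.

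**What to change.** 1. In Section 6.4, reconcile the day-based rule with the 28-dose regimen by stating how a day with one of two doses missed counts, and base the classification on the diary and tube counts. The choice of threshold belongs to the protocol team.
2. In Section 10.1, keep all treated women as the primary set and as the set for adverse events. Amend the clause that applies this set to every analysis, and add an adherent-set analysis of the Day 7 and Day 14 lavage endpoints. Require the two to agree before no difference or equivalence is claimed. State how replaced women and their replacements enter each set.
3. In the adherent set, keep women stopped for an Appendix IV toxicity, using a lavage from Day 7 or later where one exists, and otherwise report them as toxicity endpoints. Do not use the 2-hour Enrollment sample for them. Section 7.1 reserves it for the spiking studies, which Section 4.1 describes as measuring the gel itself and not endogenous activity.

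Cost: some wording and one extra analysis on data already collected. Requiring agreement slightly lowers the chance of concluding equivalence, although 18 adherent women per arm would by themselves have the planned 80% power. Selection through symptom-related skipping remains possible in the adherent set, which is why the all-treated analysis stays primary.

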## 6.5 Concomitant Medications

Enrolled participants may continue use of all concomitant medications except vaginal products(lubricants, feminine hygiene products, and vaginal drying agents) during this study. All concomitant medications (including complementary and alternative medicines, vitamins, etc.) will be recorded on applicable study case report forms. Medications used for the treatment of AEs that occur during study participation also will be recorded on applicable case report forms.

